### Primary effectiveness outcome

The primary endpoint is an “adherence score”, measuring adherence to the National Guidelines on Secondary Prevention [15]. The adherence score is partly derived from the 30 variables capturing guideline-directed CR structure and processes incorporated into the SWEDEHEART-CR registry in October 2023. Permissible values are yes/partly/no/unknown. Additionally, the adherence score will include nine process variables that measure a) patient attendance in various CR components (number of patients attending a CR programme component divided by the number of patients eligible for participation), and b) time between MI hospitalization discharge and start of different CR programme components, already audited in SWEDEHEART:

*Attendance in CR components*
Proportion of patients attending an initial CR assessment (nurse visit).Proportion of patients attending an individual visit to a physiotherapist after discharge before starting an exercise-based CR (EBCR) programme (a pre-exercise screening visit).Proportion of patients completing a 3-month EBCR programme.Proportion of patients attending an individual close-out visit to a physiotherapist after completing an EBCR programme (a post-exercise assessment visit).Proportion of patients attending a patient education programme.Proportion of patients attending a close-out CR visit with a nurse at one-year after MI.*Time (days) to start of different components of CR*7.Time from hospital discharge to initial CR assessment (nurse visit).8.Time from hospital discharge to the pre-exercise screening visit to a physiotherapist.9.Time from pre-exercise screening visit to start of EBCR programme.

The responses will be pooled at each site into an adherence score for each CR centre. The contribution of each variable to the score will be weighed depending on the importance of each measurement, based on level of recommendation in European guidelines [1].

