### Sample size calculations

As the number of CR centres is fixed, sample size calculations have been performed to estimate the difference in mean adherence score the study will be able to reveal. For this purpose, in a feasibility analysis the CR structure and process variables were collected from 8 CR centres of different sizes and geographical locations. The mean adherence score was 30.8 (standard deviation [± 2.4]) out of a maximum available score of 39. For the audit intervention, given the following presumptions:

23 out of possible 26 CR centres in each group (minimal drop-out is anticipated).Power of 80%.An alpha value of 0.05.

The study will have the power to identify a difference of ± 2.0 in adherence score between centres in cluster B (randomized to having variables on CR structure and processes incorporated in the SWEDEHEART registry) and cluster C (no new variables incorporated).

For the implementation support intervention, only centres in the lower 2 tertiles of the adherence score at baseline (approximately 17 centres) will be offered implementation support. Given the following presumptions:

14 out of possible 17 centres in each group (minimal drop-out is anticipated).Power of 80%.An alpha value of 0.05.

The study will have the power to identify a difference of ± 2.5 in adherence score between centres in cluster A (randomized to receiving implementation support) and cluster B (no implementation support).

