### Quantitative data

For baseline characteristics descriptive statistics will be used (means +/-standard deviation, medians [quartile 1, quartile 3], proportions [%] and ranges). For the primary outcome analysis, given randomized treatment assignment, total adherence scores at end of follow-up as well as change in scores between baseline and follow-up will be compared using linear regression analysis. In the case of unequal randomization concerning CR centre size (small < 75 patients/year, medium 75–150 patients/year or large > 150 patients per year), geography (6 geographical districts in Sweden, two in each stratum) or the centres belonging to a university hospital (yes/no), adjusted multivariable analysis will be performed. Results will be reported as relative treatment effects (odds ratios) with 95% confidence intervals. For secondary outcome analysis on short-term patient outcomes, the same statistical methods will be used, applying linear (continuous) or logistic (binary) regression analyses. For long-term outcomes (major adverse cardiovascular events [MACE] and total mortality) Cox proportional hazards regression models will be performed, reporting hazard ratios with 95% confidence intervals. In case of missing data, imputation will be considered. For all quantitative analyses a two-sided test of statistical significance will be used with an alpha level of 0.05.

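### The adherence score is analysed by linear regression, but its result is to be reported as an odds ratio, which that model does not give

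*Protocol article*

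**What the plan says.** The Primary effectiveness outcome section defines one number per centre: "The responses will be pooled at each site into an adherence score for each CR centre". The Sample size calculations section gives its scale: "The mean adherence score was 30.8 (standard deviation [± 2.4]) out of a maximum available score of 39".

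The Quantitative data section of the protocol article then proceeds in this order:

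1. For the primary outcome, "total adherence scores at end of follow-up as well as change in scores between baseline and follow-up will be compared using linear regression analysis".
2. Multivariable adjustment follows if randomisation leaves the groups unequal on centre size, geography or university-hospital status.
3. "Results will be reported as relative treatment effects (odds ratios) with 95% confidence intervals".
4. Only then do the secondary outcomes appear: "For secondary outcome analysis on short-term patient outcomes, the same statistical methods will be used, applying linear (continuous) or logistic (binary) regression analyses".
5. Long-term outcomes are analysed by Cox models, with hazard ratios named as their measure.

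The planning figures are differences in points. For the audit comparison, "The study will have the power to identify a difference of ± 2.0 in adherence score between centres in cluster B" and cluster C. For implementation support, "The study will have the power to identify a difference of ± 2.5 in adherence score between centres in cluster A" and cluster B. The section headed The timeline sets the interim criterion at a difference of at least 2.0 points.

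**The concern.** The treatment coefficient in a linear regression of the score is a difference in mean points. It is an absolute effect, not a relative one, and it is not an odds ratio. Getting an odds ratio for this endpoint would need a different model: a logistic model after the score is cut in two, or an ordinal model such as proportional odds. The article describes neither.

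What is at stake is the headline result. Read literally, the sentence promises a quantity that the named model cannot supply. It would also put the result on a different scale from the differences the trial was sized to detect and from the interim criterion. The economic evaluation uses guideline adherence as an effect measure in an incremental ratio whose denominator is a difference in effects, so it too needs an additive effect.

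This is not a detail left to an analysis plan. The article names an effect measure, and it is the wrong one for the model it names.

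**Working it through.** **1. Which scale was the trial planned on?** Inputs from Sample size calculations: SD 2.4, 80% power, alpha 0.05 (two-sided, per Quantitative data), 23 centres per group for B against C and 14 for A against B. For a comparison of two means by the normal approximation:

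detectable difference = SD × (z₀.₉₇₅ + z₀.₈₀) × √(2/n), with z₀.₉₇₅ + z₀.₈₀ = 1.960 + 0.842 = 2.802

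- B against C: 2.4 × 2.802 × √(2/23) = 1.98 (article: 2.0)
- A against B: 2.4 × 2.802 × √(2/14) = 2.54 (article: 2.5)

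Both figures reproduce as differences in mean points. (With the noncentral t distribution they are 2.03 and 2.64; that small gap is not part of this point.)

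**2. What does the named model return?** With the same inputs, the standard error of the difference is 2.4 × √(2/n), and the 95% interval uses the t distribution on 2n − 2 degrees of freedom.

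| Comparison | n per group | Standard error | Half-width of 95% CI | Interval at the planned difference |
|---|---|---|---|---|
| B against C | 23 | 0.71 | 2.015 × 0.708 = 1.43 | 2.0 points: 0.57 to 3.43 |
| A against B | 14 | 0.91 | 2.056 × 0.907 = 1.86 | 2.5 points: 0.64 to 4.36 |

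These can be read directly against the planned differences and the interim criterion.

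**3. Can the coefficient be turned into an odds ratio?** Exponentiating it does not do so: exp(2.0) = 7.4 and exp(2.5) = 12.2 are not odds ratios of anything in this model. An odds ratio from a cut score depends on a cut-point that the article does not give. As an illustration only, assume a normal score with mean 30.8 and SD 2.4, shifted by 2.0 points, and a cut at 32:

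- Proportion above the cut without the shift: 1 − Φ((32 − 30.8)/2.4) = 0.309
- Proportion above the cut with the shift: 1 − Φ((32 − 32.8)/2.4) = 0.631
- Odds ratio: (0.631/0.369) / (0.309/0.691) = 3.83

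Over assumed cuts from 28 to 34, the same 2.0-point shift gives odds ratios from 3.8 to 6.0, and a 2.5-point shift gives 5.4 to 10.0. No single odds ratio corresponds to either planned difference.

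**4. Could the sentence belong to another analysis?** It stands after the primary model and its adjustment rule and before the secondary outcomes. Logistic regression is first named in the sentence after it. Cox models receive their own measure. No sentence names a mean difference as the measure to be reported for the primary result.

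**The case against.** The best defence is that this is a misplaced or over-general reporting sentence. It refers to results in general, the next sentence brings in logistic models, and odds ratios suit those. Everything else about the primary comparison (the linear model, the planned differences, the interim criterion) points to a mean difference, and anyone fitting the model would notice the mismatch at once. That is probably how the sentence arose, and it limits the seriousness of the error. It does not remove it: the sentence's position ties it to the primary analysis, and if it is reassigned to the binary outcomes, the primary result is left with no stated effect measure.

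Two stronger readings are tempting, and the article supports neither.

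- A reader might infer that the sentence commits the trial to dichotomising the score, with a loss of power. For a median split of a normal score the efficiency is 2/π = 0.637, so 23 centres would act like 23 × 0.637 = 14.6, and the detectable difference would rise to 1.98/√0.637 = 2.48 points. The arithmetic is right, but it describes an analysis the protocol does not plan. An ordinal model could also give an odds ratio without any cut-point.
- A reader might infer that blood pressure and LDL-C are also promised as odds ratios, because the short-term outcomes use the same methods. That sentence carries over methods and separates linear models for continuous outcomes from logistic models for binary ones. It does not clearly carry over the reporting scale.

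**Conclusion.** The point holds as a mismatch between the stated effect measure and the stated primary model. It rests on the text of the Quantitative data section and on what a linear regression coefficient is. The recalculation confirms that the planning was done in points; the illustrative cut-points are assumptions and the conclusion does not depend on them.

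Its reach is narrow. The power calculation is not put in question by it, no change to the test or to data collection follows, and no loss of power is claimed. Because it concerns how the primary result is expressed, in an open-label trial, it should be corrected before the primary results are analysed, so that the choice of scale is not left open at that stage.

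**What to change.** Replace the odds-ratio sentence with one that ties each measure to its model:

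- **Adherence score:** mean difference in points with 95% confidence interval, for B against C and for A against B, adjusted where the section already calls for adjustment.
- **Continuous patient outcomes:** mean differences with 95% confidence intervals.
- **Binary patient outcomes (logistic models):** odds ratios with 95% confidence intervals.
- **MACE and total mortality (Cox models):** hazard ratios with 95% confidence intervals, as now stated.

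The edit should not make adjustment unconditional. The section adjusts only when randomisation turns out unequal, and changing that would alter the primary analysis, which is a separate matter.

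The cost is one sentence. Sample size, model, test and trial conduct stay as they are.

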## Background

Cardiovascular risk factor reduction and the fostering of a healthy lifestyle after an acute myocardial infarction (MI) are the most effective interventions to prevent recurrent coronary events [1]. Administering these interventions via structured and comprehensive cardiac rehabilitation (CR) programmes reduces mortality, morbidity, unplanned hospital admissions, and improves health-related quality of life [2–4]. CR is a complex intervention, combining the optimal use of cardio-protective medication, exercise training, patient education, and behavioural modification to improve lifestyle, and psychosocial counselling [5, 6]. Patient participation in CR after an MI is given the highest recommendation and level of evidence in current guidelines on cardiovascular disease (CVD) prevention [1]. However, referral rates to CR programmes are generally low and patients´ treatment target attainment is sub-optimal [7]. While treatment target attainment rates at Swedish CR centres is on average among the highest in Europe, there are considerable differences in CR service delivery between centres [8–11] and consequently, large variations in patient-level outcomes between centres [12].

The SWEDEHEART registry is a nationwide quality registry that records baseline characteristics, treatments, and outcomes of patients with MI admitted to coronary care units in Sweden [13]. Follow-up data describing secondary preventive patient-level outcomes have been collected in the CR part of the registry (SWEDEHEART-CR) since 2005 [14]. However, only a handful of variables monitoring centre-level structure and processes are included in the registry.

In 2019, a National Working Group on Secondary Prevention was commissioned by the Swedish Association of Local Authorities and Regions to author National Guidelines on Secondary Prevention for patients with coronary artery disease, aiming to decrease the variation in secondary prevention delivery and outcomes in Sweden. The guidelines were published in February 2022 [15]. In parallel with the release of CR guidelines, the SWEDEHEART-CR Working Group proposed incorporating variables into the registry to assess the recommended structure and processes outlined in the guidelines [16].

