### Secondary effectiveness outcomes

Table 2 displays secondary outcomes, encompassing both short- and long-term patient outcomes and implementation outcomes. Implementation outcomes will be based on responses gathered through the customized Normalisation Measure Development (NoMAD) questionnaire [29] and insights obtained from focus group interviews, as well as a cost-effectiveness analysis.

**Table 2 Tab2:** Secondary outcomes

Outcomes	Cluster	Measures	Data source	Timing
Short-term patient-level outcomes	All clusters	- Blood pressure (mmHg). - LDL-C (mmol/L). - Self-reported statue of health measured using EuroQol-VAS (0–10). - Self-reported smoking status (never/ prior [> 1 month smoke-free]/active) - Self-reported dietary habits (four questions with Likert scale 0–3 points, total score 0–12 points). - Self-reported physical activity (the number of days during the last week the patient has been physically active for a minimum of 30 min [at least 10 min at a time] with activity causing shortness of breath and a slightly increased pulse, corresponding to a brisk walk). - Completing an exercise-based CR programme for at least 3 months (yes/no)	The SWEDEHEART registry	Baseline and one-year after the start of intervention
		- Adherence to secondary prevention medication	Pharmaceutical registry	Baseline and one-year after the start of intervention
Long-term patient-level outcomes	All clusters	Total mortality Major adverse cardiovascular events (MACE) consisting of the following: - cardiovascular mortality - non-fatal MI - non-fatal ischemic stroke - coronary revascularization - hospitalization for new or worsening heart failure	National Patient Registry and the Cause of Death Registry	Up to 5 years after the end of the intervention
Centre-level implementation outcomes	Cluster A	- Barriers - Facilitators	Semi-structured focus group interviews	At the start and the end of implementation support period
		- Implementation cost and cost effectiveness.	A comparative health economic evaluation	At the start and the end of implementation support period

*LDL-C* low-density lipoprotein cholesterol, *VAS* visual analogue scale, *CR* cardiac rehabilitation, *MI* myocardial infarction

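### The models for short-term patient outcomes do not adjust for the centre's pre-intervention level of the same outcome, although the registry can probably supply it

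*Protocol article*

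**What the plan says.** The Quantitative data section of the protocol article compares the primary adherence score between arms by linear regression, both at end of follow-up and as change from baseline. Centre size, geography and university-hospital status enter a multivariable model only if randomisation turns out unequal on them. For patient outcomes it then says: "For secondary outcome analysis on short-term patient outcomes, the same statistical methods will be used, applying linear (continuous) or logistic (binary) regression analyses". No term for centre is named.

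Three other statements bear on this:

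- The Background says of the registry: "Follow-up data describing secondary preventive patient-level outcomes have been collected in the CR part of the registry (SWEDEHEART-CR) since 2005".
- The Background also reports "large variations in patient-level outcomes between centres".
- Table 2 (Secondary effectiveness outcomes) times the short-term patient outcomes at "Baseline and one-year after the start of intervention", and takes all of them except medication adherence from SWEDEHEART.

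Two of the secondary aims are whether audit and feedback, and implementation support, improve patient-level outcomes.

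**The concern.** In a trial that randomises centres, the precision of a patient-level contrast depends mainly on the number of centres and on how much centres differ. The number of centres is fixed. A centre's own earlier level of the outcome is likely to be the strongest predictor of its later level, and if recorded before the intervention started it cannot be affected by it. The article names a model, a covariate set and a trigger for using that set, but gives this predictor no role.

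The carried-over change comparison is a weak substitute, for three reasons:

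- Table 2 ties the timing to the start of the intervention. Most patients seen a year later are different people from those seen at baseline, so few have a within-patient change that spans the intervention.
- For completion of exercise-based rehabilitation, a patient has no value before the infarction. A baseline makes sense there only as an earlier cohort at the same centre.
- Logistic regression of a binary outcome has no change-score form.

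At stake are power for two secondary aims and protection against a chance difference in centre performance between arms. Estimated patient effects also feed the cost-effectiveness analysis.

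**Working it through.** **The plan's own figure.** It concerns the adherence score, not patient outcomes. Inputs from Sample size calculations and Quantitative data: "The mean adherence score was 30.8 (standard deviation [± 2.4]) out of a maximum available score of 39", "23 out of possible 26 CR centres in each group", 80% power, and "a two-sided test of statistical significance will be used with an alpha level of 0.05". Detectable difference = (1.96 + 0.84) × 2.4 × √(2/23) = 1.98 by the normal formula and 2.03 by the t distribution. The stated result, "The study will have the power to identify a difference of ± 2.0 in adherence score between centres in cluster B", reproduces. It uses the raw standard deviation with no baseline correlation. No power is stated for any patient outcome.

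**Inputs for patient outcomes.**

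- Centres per arm: 23 (Sample size calculations).
- Patients per centre-year: m = 10 000/78 ≈ 128 (Abstract). This is before the age, type 1 infarction and two-visit restrictions, so m = 50 is also shown.
- ICC and true between-period correlation of centre levels (c): not in the documents. Assumed ICC 0.01–0.05 and c 0.5–0.8.

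**Formulas, centre-level analysis, one pre-intervention year.**

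- Variance of a centre mean, in units of the patient variance: v = ICC + (1 − ICC)/m.
- Correlation of observed pre and post centre means: r = c × ICC / v.
- Variance relative to follow-up alone: 1 − r² with covariate adjustment, 2(1 − r) with a change score. The second exceeds 1 whenever r < 0.5.
- Power: noncentral t, two-sided 0.05, 44 degrees of freedom unadjusted and 43 adjusted, for a difference that has 80% power unadjusted.

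**One case in full.** With m = 128, ICC 0.02 and c 0.8: v = 0.02 + 0.98/128 = 0.0277; r = 0.016/0.0277 = 0.58; 1 − r² = 0.665; power 93.0%.

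**Power after adjustment, starting from 80%.**

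| m | ICC | c = 0.5 | c = 0.7 | c = 0.8 |
|---|---|---|---|---|
| 128 | 0.01 | 83% | 86% | 88% |
| 128 | 0.02 | 85% | 90% | 93% |
| 128 | 0.05 | 88% | 94% | 97% |
| 50 | 0.01 | 81% | 82% | 83% |
| 50 | 0.02 | 82% | 85% | 86% |
| 50 | 0.05 | 85% | 90% | 93% |

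At m = 128 and c = 0.8 the detectable difference shrinks by about 11%, 18% and 28% for ICC 0.01, 0.02 and 0.05. With 14 centres per arm, the number assumed for the A-versus-B score comparison, the powers are within a fraction of a point of these.

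**One low value is enough to make the gain small.** With m = 128, ICC 0.05 and c = 0.3, power is 82.7%. With m = 50, ICC 0.01 and c = 0.8, it is 82.8%.

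**Change score against covariate.** With m = 128, ICC 0.01 and c = 0.5 (r = 0.28), the change score multiplies the variance by 1.44 and adjustment by 0.92. With ICC 0.05 and c = 0.8 (r = 0.70), the factors are 0.61 and 0.52.

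**Clustering.** These gains presume that centres are the unit of analysis or that centre is modelled. If patients were analysed as independent, the design effect 1 + 127 × ICC would be 2.27 at ICC 0.01 and 7.35 at ICC 0.05. A nominal 5% test would then reject a true null about 19% and 47% of the time. A baseline covariate alone would not cure that.

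**The case against.** The strongest reply is that this is detail for an analysis plan that is not shown, and that the article does not forbid baseline adjustment. That stands in part: the full plan may contain such a model. But the article does state the model, the covariates and when they apply, and a reader following it would leave this covariate out.

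Second, a reader might infer that the plan ignores baseline altogether. The documents do not support that. The reference to the same methods can be read as carrying over the change comparison, and the timing in Table 2 can be read as an earlier and a later cohort. The baseline's role is therefore unclear rather than absent, and what is missing is a baseline-adjusted model.

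Third, a reader might infer that stable centre differences are known to sit in the residual variance. The Background calls the variation large and says nothing about its stability. The national guideline appeared in February 2022, so earlier years may predict later ones less well. The named regression also has no centre term. Unless clustering is modelled, the immediate fault would be standard errors that are too small, not an inflated residual.

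Fourth, that the registry holds every named outcome for past years is a sound inference from the 2005 statement and the data-source column of Table 2, but not an explicit statement. The power figures come from a linear calculation. For logistic models they are only a guide, and adjustment there also changes the odds ratio being estimated.

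**Conclusion.** The point holds as a worthwhile improvement to the secondary analyses. No model adjusts short-term patient outcomes for the centre's pre-intervention level, and a change score is at best a partial and sometimes harmful substitute.

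A reader might infer bias from this. There is none from the omission itself: centres are randomised, and the cost is precision and uncorrected chance imbalance. A reader might also expect a large gain in every case, and the documents cannot support that either. Power of 83–97% at 128 patients per centre-year, and 81–93% at 50, rests on assumed ICC 0.01–0.05, assumed between-period correlation 0.5–0.8, and an analysis that respects clustering. If either assumed value is low, the gain may be only 1–3 points. The primary adherence-score comparison is not affected.

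**What to change.** For each short-term patient outcome taken from SWEDEHEART, in both the B-versus-C and the A-versus-B comparison, pre-specify as the main analysis a model that:

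1. respects clustering, by regression on centre summaries or a centre random effect; and
2. includes as a covariate the centre's mean or proportion of the same outcome, among eligible patients whose outcome was recorded before October 2023, whether or not imbalance is seen.

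State that Table 2's baseline means this centre cohort, or, where it means the patient's own earlier value, say so outcome by outcome. Smoking is recorded in three categories, so state how it is made binary. For logistic models, state which odds ratio is the target.

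The cost is wording in the analysis plan, a longer extract from the same registry and one degree of freedom. No new data collection is needed. The extract would also give the ICC and the between-period correlation, which the documents lack.

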**Methods:**

The study is an open-label cluster-randomized effectiveness-implementation hybrid trial including all 78 cardiac rehabilitation centres (attending to approximately 10 000 MI patients/year) that report to the SWEDEHEART registry. The centres will be randomized 1:1:1 to three clusters: 1) reporting cardiac rehabilitation structure and process variables to SWEDEHEART every six months (audit intervention) and being offered implementation support to implement guidelines on secondary prevention (implementation support intervention); 2) audit intervention only; or 3) no intervention offered. Baseline cardiac rehabilitation structure and process variables will be collected. The primary outcome is an adherence score measuring centre-level adherence to secondary prevention guidelines. Secondary outcomes include patient-level secondary prevention risk factor goal attainment at one-year after MI and major adverse coronary outcomes for up to five-years post-MI. Implementation outcomes include barriers and facilitators to guideline adherence evaluated using semi-structured focus-group interviews and relevant questionnaires, as well as costs and cost-effectiveness assessed by a comparative health economic evaluation.

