### Randomization

Centres will be randomized 1:1:1 to three clusters (A, B and C). Randomization will be stratified by geographical healthcare district (two districts in each stratum). Randomization will be performed by an independent organisation not involved in the study to avoid site-selection bias.

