### Data analysis

In the primary outcome analysis of the audit intervention, CR centres in clusters B and C will be compared. All CR centres that have responded to the CR structure and process variables will be included in the analysis. For the primary outcome analysis of the implementation support intervention CR centres in clusters A and B will be compared. All CR centres that have i) provided answers to the structure and process variables and that ii) have scores in the lower two tertiles of the adherence score at baseline will be compared. Our analyses will assume intention-to-treat principles by treating intervention assignment as randomized regardless of whether the intervention had uptake within the practice. If not all centres in cluster A accept implementation assistance, a per-protocol analysis will be performed including only those centres in study group A that accept implementation assistance.

For the secondary analyses on patient outcomes, all patients that attended at least two follow-up visits within CR will be included. For the outcome analysis of the audit intervention patients followed at CR centres in clusters B and C will be compared. For the outcome analysis of the implementation support intervention patients followed at CR centres in clusters A and B will be compared. A per-protocol analysis will be performed including only patients belonging to CR centres in cluster A that accept implementation assistance.

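### Patient-level outcomes of a centre-randomised trial are assigned linear, logistic and Cox regression with no allowance for centre, so as written their standard errors are too small

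*Protocol article*

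**What the plan says.** The Randomization section makes the centre the unit of allocation: "Centres will be randomized 1:1:1 to three clusters (A, B and C"). The word cluster here means a trial arm, so it does not signal an adjustment for clustering.

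For the primary outcome, which has one adherence score per centre, the Quantitative data section states that "total adherence scores at end of follow-up as well as change in scores between baseline and follow-up will be compared using linear regression analysis".

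For patient outcomes, the unit compared is the patient. Under Data analysis: "For the outcome analysis of the audit intervention patients followed at CR centres in clusters B and C will be compared", with a parallel sentence for A against B. The Quantitative data section then says that for short-term patient outcomes "the same statistical methods will be used, applying linear (continuous) or logistic (binary) regression analyses". For events and mortality it says that "Cox proportional hazards regression models will be performed, reporting hazard ratios with 95% confidence intervals". It closes with: "For all quantitative analyses a two-sided test of statistical significance will be used with an alpha level of 0.05".

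The only adjustment named is for centre size, geography and university-hospital status, and only if randomisation turns out unequal on them. No section mentions a random effect, GEE, cluster-robust variance, frailty term, ICC or design effect.

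**The concern.** Linear regression suits the adherence score because each centre contributes one observation and centres were randomised independently. That justification goes when the method is moved to patients. Patients at one centre share its staff, routines and catchment, and they were all allocated together. A model without a centre term counts every patient as a separate piece of evidence about the arm effect.

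The article's own rationale makes a zero ICC hard to defend. The Background reports "large variations in patient-level outcomes between centres" and links this to differences in service delivery.

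At stake are the two secondary aims that ask whether audit, or implementation support, improves patient outcomes. Intervals that are too narrow could turn ordinary between-centre variation into an apparent benefit or harm.

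**Working it through.** **1. The plan's own figure.** The only sample-size statement concerns the centre-level score (Sample size calculations: SD 2.4, 80% power, two-sided alpha 0.05). The detectable difference is 2.4 × (1.960 + 0.842) × √(2/n).

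- n = 23 per group: 1.98 (2.03 with the t distribution), against a stated 2.0.
- n = 14 per group: 2.54 (2.64 with t), against a stated 2.5.

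Both are reproduced by the normal formula, within rounding. They use one value per centre, so clustering of patients does not enter. No such figure is given for patient outcomes.

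**2. Patients per centre.** The abstract gives "all 78 cardiac rehabilitation centres (attending to approximately 10 000 MI patients/year"). So m = 10 000 / 78 = 128 per centre-year, and 78 / 3 = 26 centres per arm. This counts all MI patients. The analysis set is limited to type 1 MI at age 18–79 (Study setting and recruitment) with two or more follow-up visits (Data analysis). For a one-year cohort 128 is therefore an upper figure, and m = 50 is taken as a low alternative (an assumption).

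**3. Formulas.** Design effect: DE = 1 + (m − 1) × ICC. The correct standard error is √DE times the unadjusted one. Real two-sided type I error of the unadjusted test: 2 × [1 − Φ(1.96/√DE)].

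Example at m = 128.2 and ICC 0.01: DE = 1 + 127.2 × 0.01 = 2.27; √DE = 1.51; 1.96/1.51 = 1.30; type I error 19.4%.

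**4. Results.** The article gives no ICC, so the values below are assumptions.

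| Assumed ICC | DE, m = 128 | √DE, m = 128 | Type I error, m = 128 | Type I error, m = 50 |
|---|---|---|---|---|
| 0.001 | 1.13 | 1.06 | 6.5% | 5.6% |
| 0.005 | 1.64 | 1.28 | 12.5% | 7.9% |
| 0.01 | 2.27 | 1.51 | 19.4% | 10.8% |
| 0.02 | 3.54 | 1.88 | 29.8% | 16.4% |
| 0.05 | 7.36 | 2.71 | 47.0% | 29.1% |

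**5. What moves these figures.**

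- Pooling years raises them. With three years (m = 385), ICC 0.001 gives 9.6% and ICC 0.01 gives 37%.
- Unequal centre sizes raise them, and the article's size bands run from under 75 to over 150 patients a year. With an assumed coefficient of variation of 0.6, DE = 1 + ((1 + 0.6²) × m − 1) × ICC. At m = 128 that gives 23.6% at ICC 0.01 and 52.8% at ICC 0.05.

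**6. Check by simulation.** Unadjusted tests were simulated with 23 centres per arm, 128 patients per centre and no treatment effect. At ICC 0.01 they rejected in 19.8% of runs for both a continuous and a binary outcome. At ICC 0.05 they rejected in 47.7% and 47.6%. A binary stand-in for cardiovascular events (15% event rate, an assumption) gave 6.0%, 12.0% and 19.1% at ICC 0.001, 0.005 and 0.01. The Cox model itself was not simulated.

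**The case against.** The strongest objection is that the article names model families, not variance estimators. Linear, logistic and Cox regression can each carry a robust variance, a random intercept or a frailty term. The text never says that patients are treated as independent, and a full protocol or analysis plan may settle the matter. It stands that independence is inferred. It does not dispose of the point, because the article is not silent: it fixes the method, the reporting of intervals and the alpha level, and it takes the method over from an analysis in which clustering cannot arise. If a fuller plan does account for centre, this section misdescribes the analysis and should be amended anyway.

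Second, the inflation depends on an ICC that the article does not give. This also stands. A reader might infer that the false-positive rate is far above 5% for every patient outcome. The Background remark on variation supports a non-zero ICC but names no outcome and gives no value. At an ICC near 0.001, which is plausible for mortality or cardiovascular events, the excess is small unless years are pooled.

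Third, a reader might carry the 14 to 17 centres from the sample size section into the patient-level comparison of A and B. The Data analysis section restricts only the centre-level comparison to the lower two baseline tertiles. Its sentence on patients has no such restriction.

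Fourth, a reader might conclude that the cost-effectiveness result is wrong. The ICER is a ratio of point estimates and also uses guideline adherence as an effect measure. Ignoring clustering mainly affects the precision attached to the patient effects.

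The conditional adjustment for size, geography and university status does not answer the point. A few centre covariates, used only in case of imbalance, leave the remaining within-centre correlation in place.

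**Conclusion.** The point holds for the secondary patient-level outcomes. Applied as written, the named models give standard errors that are too small by a factor of √DE, and a type I error above 5%. Over the assumed ICC range of 0.001 to 0.05, the real error runs from about 6.5% to 47% at 128 patients per centre and from about 5.6% to 29% at 50. Where in that range an outcome falls depends on its ICC, the size of the analysis set and the number of years pooled, and the article states none of these.

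The primary adherence score, its analysis and its power statement are unaffected. For cost-effectiveness, only the uncertainty around the patient effects is affected. The article does not support a claim that all patient-level findings will be badly inflated. It does support the claim that the stated method does not match the unit of randomisation and should be corrected before analysis.

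**What to change.** Amend the Quantitative data section so that all patient-level models account for centre:

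- Continuous and binary outcomes: linear or logistic mixed models with a random centre intercept, or GEE clustered on centre, with a small-sample correction.
- Cardiovascular events and mortality: Cox models with centre-level robust variance or a shared frailty.
- Base inference on the number of centres that actually contribute to each comparison (up to 26 per arm), and report the ICC for each outcome.

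No new data are needed, since the Data protection section confirms that patient records identify the follow-up centre. The price is wider intervals for the secondary outcomes: at 128 patients per centre, by a factor of 1.06 at ICC 0.001 and 2.71 at ICC 0.05. The 3333 or so patients per arm (26 × 128.2) would then carry the information of about 2957 and 453 independent patients respectively.
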